### Blinding

Given the nature of the intervention, only the outcome assessors involved in the data collection and data analysts are blinded to the study groups and unblinding will not occur. Nevertheless, study participants are told that activities are individualized and not informed of the different study arms. Interventions are also scheduled to avoid contact between participants of different study arms and participants are asked to not describe their activities to those outside of their exercise group. Although it is not possible to blind program instructors to the intervention that they deliver, instructors are not made aware of the study aim and hypothesis.

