#### Blood marker measures

Systemic blood markers to be measured are serum TNF-α [35], BDNF [34], and NF-L [37, 38]. Blood samples are collected by a licensed phlebotomist at an off-campus location by venipuncture from the antecubital fossa to a vacutainer tube with no additive. The samples are allowed to clot and then centrifuged at 2,000 g for 30 min at 4 °C. Serum is aliquoted, transported to campus on ice, and stored at -80 °C within two hours of collection. Concentrations of all analytes will be measured using assays with appropriate sensitivity and reliability. Given low concentrations of NF-L, ultrasensitive assays will be considered for analysis in addition to more standard enzyme-linked immunosorbent assays. Assays will be run by a study team member in a preliminary analysis once a third of the projected sample has completed the study. Additional samples will be run in a single, batched analysis following completion of all data collection. Further blood markers linked to MS disease progression and exercise (e.g., interleukin-6) may be added to the analysis protocol if sample volume permits.

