#### Statistical analysis and sample size calculation

Baseline data collection will include both demographic and MS-related information (Table 3). The primary statistical analysis will compare T25-FWT performance at the post-intervention time point between the three study arms using ANCOVA (analysis of covariance) with a between-groups factor (task-oriented, generalized resistance and aerobic exercise, stretching control) and adjusting for baseline T25-FWT performance [28]. Planned pairwise comparisons will directly test differences between each study arm. Comparison of the secondary outcome and all other outcome measures at the post-intervention time point across study arms will follow the primary analysis methods (i.e., ANCOVA adjusting for relevant baseline measure). Exploratory analysis of change in outcome measures across all time points and between study arms will use a linear mixed effects model with Time point, Study arm, and Baseline T25-FWT performance as fixed factors. Participant will be a random factor. The models will account for dependencies/correlations resulting from repeated measurements. Final exploratory analyses will re-run all statistical tests with data disaggregated by sex [70–72]. For all statistical tests, the alpha will be 0.05. Point and 95% confidence interval estimates for study arm differences will be determined. Participants will be analyzed in the study arm to which they were randomized (i.e., intention-to-treat principle). Multiple imputation will be used to minimize biased estimates from missing data with the analysis based on a missing at random assumption [73]. We will conduct an interim analysis when 50% of the sample has completed study procedures. This interim analysis will allow dissemination (i.e., conference presentations) of preliminary findings. There is no stopping rule for the trial because no serious adverse events from the intervention are anticipated.

**Table 3 Tab3:** Baseline data collection variables

Variables
Age (years)
Sex
Gender (optional)
Height
Weight
BMI
Type of MS
Year of MS onset (e.g., first symptom)
Year of MS diagnosis (by a neurologist)
Most recent relapse (month/year)
Patient Determined Disease Steps
Walking aid or assistive devices
More affected side (upper and lower body)
Medications (including disease-modifying therapy)
29-Item Multiple Sclerosis Impact Scale
Clinical MRI availability
Other health conditions
Employment/Work status
Typical Day
Fall history past 7 days

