#### Monitoring and data management

This study, including the participant consent form, has received ethical approval from the University of Regina Research Ethics Board (REB file 2021 − 197). Given that this is a low-risk intervention, no data monitoring review committee is required; however, the University of Regina Research Ethics Board has the authority to audit the study at any time to ensure compliance with approved protocols. Meetings of the research team will be held every three to six months to discuss day-to-day management and organisation of the study, including participant recruitment, delivery of the intervention, and participant monitoring.

All data, including the final trial dataset, is de-identified, coded and stored on a University of Regina server that is accessed only by members of the study team from password-protected computers. Physical copies of the data recording sheets are stored in locked filing cabinets at the University of Regina. All data is checked regularly by the study team to ensure protocols and ethical guidelines for data collection and analysis are followed. Study-related documents will be archived at the University of Regina at the end of the study and stored for a minimum of five years according to current ethical guidelines.

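### The half-sample interim analysis serves only conference presentation and is not limited to pooled results, so it may reveal which arm is ahead while up to half of the primary data are outstanding

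*Protocol article*

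**What the plan says.** Under Statistical analysis and sample size calculation, the protocol article states: "We will conduct an interim analysis when 50% of the sample has completed study procedures". The next sentence gives the only reason for it: "This interim analysis will allow dissemination (i.e., conference presentations) of preliminary findings". No action follows from the look. The same paragraph says: "There is no stopping rule for the trial because no serious adverse events from the intervention are anticipated". No sample size re-estimation is described, and Monitoring and data management says that "no data monitoring review committee is required".

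The Blinding section sets out how bias is to be controlled. Outcome assessors and "data analysts are blinded to the study groups and unblinding will not occur". For the two groups that cannot be blinded in the usual sense, the plan withholds information instead: "study participants are told that activities are individualized and not informed of the different study arms", and "instructors are not made aware of the study aim and hypothesis". The limitations paragraph of the Discussion accepts that this blinding is not beyond dispute. It relies on scheduling and on limiting what instructors are told.

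The article nowhere says that interim results will be pooled, kept under arm codes, kept from instructors, or held until follow-up ends.

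**The concern.** An interim analysis normally earns its risks by supporting a decision on safety, futility or sample size. This one supports none. Its output is meant for an audience outside the trial, at a point when many participants are still to be treated or assessed.

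The main question is which of three exercise approaches gives the faster walk, so findings presented by arm would show which arm appears to lead. Instructors know what they deliver. If they learn that their arm is ahead or behind, their effort and encouragement could change. Later participants could learn both that different arms exist and which one looks better. Recruitment draws on local organisations, healthcare facilities and a provincial MS research database (Study participants), and the Dissemination plan aims conferences at researchers and healthcare providers, so such news could plausibly travel back. The primary outcome, the Timed 25-Foot Walk Test, measures fast walking speed, which can reasonably be expected to respond to motivation. Bias that enters the second half of the data this way cannot be removed in the analysis.

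**Working it through.** **Inputs.** From Statistical analysis and sample size calculation: 63 participants, 21 per arm, d = 0.95 (95% CI 0.2–1.7), two-sided 5%, power 85%, interim at 50%. From Table 2: post-intervention assessment in week 13, retention in week 18. From Trial status: enrolment from May 2022, about 30% recruited, completion expected by January 2025.

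**1. The plan's own figure.** For a two-sample t-test with n per arm, the noncentrality is d·√(n/2) on 2n − 2 degrees of freedom. At n = 21 this is 0.95 × √10.5 = 3.08, giving 85.2% power; n = 20 gives 83.3%. The stated 21 per arm is reproduced.

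**2. Power at the interim.** 50% of 63 is 31.5, about 32 participants or 10–11 per arm.
- n = 10: noncentrality 0.95 × √5 = 2.12, power 52.0%.
- n = 11: noncentrality 0.95 × √5.5 = 2.23, power 56.4%.

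**3. Precision.** The 95% CI half-width for a pairwise difference, in SD units, is t(0.975, 2n − 2) × √(2/n).
- n = 10: 2.101 × 0.447 = 0.94.
- n = 11: 2.086 × 0.426 = 0.89.
- n = 21: 2.021 × 0.309 = 0.62.

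An observed difference exactly at the planned 0.95 SD would have an interval of 0.01 to 1.89 with 10 per arm, against 0.33 to 1.57 with 21. These figures ignore baseline adjustment, which would be expected to narrow the interim and final intervals by a similar factor.

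**4. Could the apparent leader be wrong?** As an assumption, take a true d of 0.5, which lies inside the plan's quoted interval. The chance that the observed difference has the wrong sign is Φ(−0.5/√(2/n)): Φ(−1.12) = 13% with 10 per arm, and Φ(−1.62) = 5% with 21.

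**5. How much is still to come.** The article does not state recruitment at the interim, so this step rests on an assumption: the status statement dates from about August 2023, the month of the amendment.
- Recruited so far: 0.30 × 63 ≈ 19 in about 15 months, or 1.27 per month.
- Rate needed to finish by January 2025, with last enrolment about September 2024: 44/13 ≈ 3.4 per month.
- Weeks 0 to 18 inclusive are 19 weeks, about 4.4 months. Participants in progress when 32 have finished: 1.27 × 4.4 ≈ 6, or 3.4 × 4.4 ≈ 15.
- Not yet recruited at that point: 63 − 32 − 6 = 25, or 63 − 32 − 15 = 16.
- Past week 13 but not yet week 18 (5 weeks, about 1.15 months): 1.27 × 1.15 ≈ 1.5, or 3.4 × 1.15 ≈ 4. Primary assessments outstanding: 31 − 1.5 ≈ 30, or 31 − 4 = 27, out of 63.

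These counts apply on the day of the look. A conference comes later, so fewer would be outstanding by then. Half is therefore an upper limit.

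**The case against.** The strongest reply is that the text does not say what will be shown. Preliminary findings could be pooled, or arms could appear under codes, and a condensed article may leave such procedures to a fuller document. This stands as a limit: presentation by arm is an inference. But the article does commit to public release and sets no restriction on it.

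A reader might go further and infer that the interim contradicts the statement that unblinding will not occur. The documents do not support that. Blinding there concerns knowledge of the study groups, and an aggregate result reveals no individual's allocation. Analysts can work on coded arms. The walk test is administered by a blinded physical therapist, who could not favour one arm without knowing who is in it. The risk therefore runs mainly through instructors and later participants.

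It is also fair to say that the three arms and the directional hypothesis are already public through the registration and this article. What the interim would add is which arm appears to be winning.

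Three further inferences should be resisted:
- **Type I error.** With no stopping and no adaptation, the earlier look does not change the level of the final 5% test. Nothing says that a significant result at either look would count as success.
- **Overstated effects.** A half-sample estimate is imprecise but not inflated in itself. Inflation arises among results selected for significance, and the article does not make presentation depend on significance.
- **The early blood assays.** The article says: "Assays will be run by a study team member in a preliminary analysis once a third of the projected sample has completed the study". It states neither a comparison by arm nor a presentation of those data, so the point does not extend to them.

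**Conclusion.** The concern holds in a limited form and should be fixed. The plan commits to a half-sample analysis whose sole stated use is public presentation, attaches no decision to it, and does not confine it to pooled or arm-coded results. If shown by arm, it would undercut the plan's own measures for participants and instructors while up to half of the primary data may be outstanding: about 27 to 30 of 63 on the day of the look, under the recruitment assumptions above. What would be released is weak evidence, with intervals about one and a half times as wide as at the end (0.94/0.62 = 1.5; 0.89/0.62 = 1.4) and 52–56% power for the planned effect.

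This rests on three assumptions: presentation by arm, continuing enrolment or follow-up at that time, and some sensitivity of a fast-walk test to motivation. The size of any resulting bias cannot be calculated from the documents. Sample size, planned power and the level of the final test are unaffected.

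**What to change.** In Statistical analysis and sample size calculation, either delete the comparative interim analysis or state that its results will be withheld. Then add a release rule along these lines: until the last participant's post-intervention primary assessment is complete and the primary data are locked, only pooled baseline, recruitment, adherence and safety data, not split by arm, may be presented outside the trial.

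Tying release to the last primary assessment protects the outcome on which the trial will be judged. It does not cover retention visits that fall after the lock.

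The change is wording only. The sample size stays at 63 and power at 85%. The price is giving up an early conference abstract with arm-level results; an abstract on design, feasibility or baseline characteristics remains possible.

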The overall goal of this work is to accelerate the development of improved exercise approaches for PwMS by characterizing the distinct functional effects and mechanistic underpinnings of task-oriented exercise for walking. The objective of the study is to compare the effect of task-oriented exercise against generalized resistance and aerobic exercise and a stretching control intervention on walking and CNS function in PwMS. Our primary hypothesis is that task-oriented exercise focused on walking will result in greater improvements in walking speed in PwMS than the alternate exercise interventions. We postulate that these task-oriented effects on walking speed will be accompanied by increases in corticospinal excitability for the ankle dorsiflexors that are not elicited by the other exercise approaches. Finally, we expect that exercise effects on musculoskeletal and aerobic fitness and global markers of CNS health will be similar across task-oriented and generalized resistance and aerobic exercise approaches, but greater than effects elicited by the stretching control intervention.

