Fall history complete/triggers
Godin Physical Activity/Leisure Questionnaire
TMS contraindications

Notes: BMI: body mass index; MS: multiple sclerosis; MRI: magnetic resonance imaging; TMS: transcranial magnetic stimulation

The sample size was calculated based on the primary hypothesis and outcome. Most prior work studying the effects of exercise on walking speed has used interventions that cannot be distinctly classified as task- or non-task-oriented exercise, and has not compared the effects of different types of exercise [21, 22]. Thus, our sample size calculation is informed by a study in which combined gait and dual-task training resulted in a greater improvement in walking speed than lower-extremity resistance exercise in PwMS [28]. The combined gait and dual-task training (n = 26) yielded an average improvement in walking speed of 21.4%, while the resistance exercise (n = 12) yielded only a 2.5% change (i.e., null) [28]. The effect size describing the difference between groups in change in walking speed was large and significant (Cohen’s d = 0.95, 95% CI: 0.2–1.7) [28]. As the proposed intervention is longer and of higher volume than the prior work [28], we expect an effect size of similar or greater magnitude. Thus, based on the effect size reported in the prior work [28], we determined that a total of 63 participants (n = 21 per study arm) will be required to detect a clinically important mean difference of 20% in walking speed on the T25-FWT [59, 74] between study arms at the post-intervention time point with a two-sided significance level of 5%, a power of 85%, and equal allocation to the three arms of the trial.

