## Discussion

There are approximately 90,000 PwMS in Canada [3] with the highest prevalence in the Prairie Provinces including Saskatchewan [76]. Beyond the direct effects experienced by PwMS, the economic burden on society via lost years of working life and healthcare costs is substantial [77]. The idea of a paradigm shift in MS healthcare towards the use of “exercise as medicine” has been proposed as a means to improve outcomes and alleviate the economic burden of MS [16]. Yet, ongoing work suggests that PwMS have difficulties engaging in physical activity and exercise [78, 79] and that there are limited exercise services that are specialized to their needs and goals [80]. Moreover, a “best” exercise approach for PwMS to optimize walking function and counter pathophysiological changes in the CNS is not well characterized. Research that compares exercise approaches and considers underlying CNS mechanisms in PwMS will advance the field towards providing targeted exercise prescriptions that maximize functional gains and related neural changes.

The positive effects of exercise on symptom management and overall health and wellness provide sufficient rationale for it to be recommended and prescribed to PwMS [20]. However, if a person with MS has a certain number of hours per week to dedicate to an exercise routine, currently it is not clear on what type of exercises that time is best spent. It is likely that the full power of exercise to benefit PwMS will not be realized without efforts to optimize an exercise approach to both the specific goals of PwMS and to the pathophysiology of the disease. Task-oriented exercise is an evidence-based approach to support functional gains and underlying neuroplasticity in people with stroke [14]. Although it is not a typical approach to exercise prescription for PwMS and other neurodegenerative conditions, initial findings suggest that it has potential for improving valued motor functions, such as walking [14]. Nevertheless, other work using a more generalized exercise approach has also demonstrated improvements in walking function compared to a non-exercise control intervention [12]. Here, we designed a novel and comprehensive study to determine the distinct effects of a task-oriented exercise approach relative to a more generalized exercise approach for improving walking function and eliciting neural changes in PwMS.

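### The 85% power is that of one pairwise comparison with complete data; at the same effect size, power for the primary hypothesis (better than both other arms) is about 77%, and no success rule is stated

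*Protocol article*

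**What the plan says.** All of this is in the protocol article.

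- **Hypothesis (Background, last paragraph).** The primary hypothesis is that "task-oriented exercise focused on walking will result in greater improvements in walking speed in PwMS than the alternate exercise interventions". The plural covers generalized resistance and aerobic exercise as well as the stretching control; the sentence before it names both.
- **Sample size (Statistical analysis and sample size calculation).** The calculation is said to rest on the primary hypothesis and outcome. Its effect size comes from one earlier two-group study (Cohen's "d = 0.95, 95% CI: 0.2–1.7"). The target is a "clinically important mean difference of 20% in walking speed on the T25-FWT" between arms, "with a two-sided significance level of 5%, a power of 85%, and equal allocation to the three arms of the trial", giving 21 per arm. No drop-out rate or inflation appears.
- **Analysis (same section).** A three-arm ANCOVA of post-intervention T25-FWT adjusts for baseline. "Planned pairwise comparisons will directly test differences between each study arm". "For all statistical tests, the alpha will be 0.05". Missing data are to be multiply imputed. The section does not say which contrasts must be significant for the primary hypothesis to count as confirmed, nor that the overall test must be significant first.

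**The concern.** A sample size tied to a hypothesis with two comparators should carry the power to confirm that hypothesis. A single d from a two-group study, with 85% power, looks like the power of one contrast. If so, a reader will credit the trial with more power for its main claim than it has.

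The missing success rule makes this worse, because it leaves open what counts as a positive trial. A win over stretching alone could be reported as confirming the hypothesis. Yet the gap named in the Background is whether task-oriented exercise is superior to other exercise approaches, which turns mainly on the generalized arm.

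**Working it through.** **Inputs from the protocol:** d = 0.95, two-sided alpha 0.05, power 85%, 1:1:1 allocation, 63 participants (21 per arm). **Assumptions made here:** the same d against each comparator in the base case, and every loss rate and correlation below.

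**1. Reproduce the stated figure.** The power of a two-sample t-test comes from the noncentral t with df = 2n − 2 and noncentrality d√(n/2).
- n = 21: 0.95 × √10.5 = 3.08, df 40, power 85.2%.
- n = 20: 0.95 × √10 = 3.00, df 38, power 83.3%.

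So 21 is the smallest n that reaches 85%, and 3 × 21 = 63 leaves no margin. Other routes do not give 63:

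| Method | Total for 85% | Power at 63 |
|---|---|---|
| One t-test, alpha 0.05 | 63 | 85.2% |
| Three-arm F-test, means (0.95, 0, 0), f = 0.448 | 60 | 88.4% |
| Three-arm F-test, means (0.95, 0.475, 0), f = 0.388 | 78 | 77.1% |
| One t-test, alpha 0.05/2 | more than 63 | 77.0% |
| One t-test, alpha 0.05/3 | more than 63 | 71.7% |

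**2. Power to beat both arms.** The two task-oriented contrasts share an arm, so their estimates correlate at 0.5. With pooled variance on 3n − 3 df and critical value c, both are significant in the right direction with probability

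E[ Φ(Z + d₁√n − cS√2) × Φ(Z + d₂√n − cS√2) ],

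where Z is standard normal and S² is chi-square on 3n − 3 df divided by its df.
- d₁ = d₂ = 0.95, n = 21: **77.0%** (76.0% with separate two-sample variances).
- For scale, 85% on both contrasts would need 25 per arm (75 in total).

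**3. Sensitivity to the effect against stretching.** With d = 0.95 against generalized exercise and 1.2 against stretching, n = 21: 84.3%.

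**4. Sensitivity to ANCOVA.** The quoted d describes change in walking speed. With equal variances and baseline-to-post correlation r, change-score variance is 2σ²(1 − r) and ANCOVA residual variance is σ²(1 − r²). Their ratio is (1 + r)/2, so the effective d is 0.95/√((1 + r)/2).

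| Assumed r | Effective d | Power for both, n = 21 |
|---|---|---|
| 0.9 | 0.975 | about 79% |
| 0.8 | 1.001 | about 82% |
| 0.7 | 1.030 | about 84% |

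**5. Sensitivity to loss.** Base case, d = 0.95 against each arm:

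| Analysed per arm | Assumed loss | One contrast | Both contrasts |
|---|---|---|---|
| 21 | 0 | 85.2% | 77.0% |
| 19 | 2/21 = 10% | 81.3% | 71.7% |
| 18 | 3/21 = 14% | 79.1% | 68.7% |
| 17 | 4/21 = 19% | 76.6% | 65.5% |

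**6. Error rates with no true difference, 21 per arm (simulation).**
- At least one of three contrasts significant: 12.1–12.2%.
- At least one of the two task-oriented contrasts significant, either direction: about 9.0%.
- At least one of those two significant in favour of task-oriented exercise: about 4.5%.
- Any of three, read only after a significant overall F-test: 5.0%.
- Both task-oriented contrasts significant in its favour: 0.5%.

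**The case against.** **The arithmetic is right.** It is. The section speaks of detecting a difference between arms and nowhere claims joint power. A reader might infer a calculation error, but the stated figure reproduces exactly. What stands is that the same paragraph ties the figure to a hypothesis with two comparators, and the figure is not the power for that hypothesis.

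**Low power and inflated error cannot both apply.** This is correct. A reader might infer that the trial has 77% power and a 12% error rate together. The two belong to different success rules. If both contrasts are required, no alpha adjustment is needed and the cost is power. If either task-oriented contrast suffices, the chance of at least one success at d = 0.95 is about 94%, and error is the issue. Even then the 12% includes generalized exercise versus stretching, which is outside the primary hypothesis, and results in the wrong direction. The protocol fixes neither rule.

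**The 77% is conditional.** Also correct. The Discussion notes that "other work using a more generalized exercise approach has also demonstrated improvements in walking function compared to a non-exercise control intervention", which supports a larger gap to stretching than to generalized exercise. ANCOVA may also add precision. Taken singly over the ranges shown, these bring joint power to 79–84%, still short of 85%. Taken together (effective d from step 4 with 1.2 against stretching), they give about 86–90% with complete data, and r below about 0.68 alone would pass 85%. The protocol's calculation takes credit for neither. The Discussion sentence also cuts the other way, since a generalized arm that improves walking narrows the contrast that matters most.

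**Contrast hierarchy and multiplicity often sit in an analysis plan.** True, and their absence alone would be no finding. The point here is what the article does state: a power tied to the primary hypothesis, and 0.05 for every test.

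**Conclusion.** The point holds, at the level of something that should be fixed and not a flaw that undermines the design. The 85% is per-contrast power with all 63 participants analysed. For the hypothesis as the Background words it, power is about 77% if d is 0.95 against each comparator and ANCOVA brings no further gain. It is about 84% with d = 1.2 against stretching, or about 79–84% with an assumed baseline-to-post correlation of 0.9–0.7.

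A reader might take the 66–72% under loss as the trial's expected power. The documents do not support that: they give no drop-out rate, and 17 to 19 analysed per arm is an assumption. They show only that nothing was added to the bare requirement. Multiple imputation limits bias but does not bring back the lost information.

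The familywise figures (about 12% over three contrasts, about 9% over the two task-oriented ones) hold only if one significant contrast could be claimed as success. They do not apply if both are required.

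**What to change.** 1. **State the success rule.** The primary claim is made only if task-oriented exercise is significantly better than both generalized exercise and stretching, each at two-sided 0.05. Because both are required, no alpha split is needed.
2. **Make generalized exercise versus stretching a secondary comparison.**
3. **Restate the power.** 85% for each contrast with complete data, and about 77% for the primary hypothesis with d = 0.95 against each arm. Add about 72%, 69% and 66% for 19, 18 and 17 analysed per arm, labelled as assumptions. Any credit for ANCOVA or for a larger effect against stretching should be shown with the value assumed.
4. **Keep 63 participants.**

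The cost is a few sentences and a less favourable stated power. Enrolment was about 30% complete at the time of the article, so the rule can be fixed before the interim analysis planned at 50% of the sample shows any outcome results.
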